### Discontinuation of study intervention

If the subject discontinued using curcumin, this will translate to discontinuation from the study, and remaining study procedures will follow as indicated by the protocol. If a clinically significant finding is identified by the study investigators (including, but not limited to changes from baseline) after enrollment, the investigator or qualified designee will determine if any change in participant management is needed. Any new clinically relevant finding will be reported as an adverse event (AE).

The data to be collected at the time of study intervention discontinuation will include the following: (1) reason for discontinuation of medication, (2) any side effects or symptoms experienced, and (3) cumulative dosage of curcumin ingested at that time.

In addition, participants are free to withdraw from the study at any time upon request, the study investigator may also discontinue or withdraw the participant from the study if any of the following occurred: (1) significant study intervention non-compliance, (2) if any clinical adverse event (AE), laboratory abnormality, or other medical condition or situation occurs such that continued participation in the study would not be in the best interest of the participant, (3) disease progression which requires discontinuation of the study intervention, (4) if the participant meets an exclusion criterion (either newly developed or not previously recognized) that precludes further study participation, and (5) participant is unable to receive curcumin tablets for 12 weeks. Study investigators will document these reasons as Case Report Form.

### Replacements

Subjects will be replaced with other subjects under the following conditions: (1) if they signed an informed consent form, randomized but did not receive study intervention; (2) if they signed the informed consent from, randomized, received the study intervention, and subsequently withdrew or withdrawn/discontinued from completing the study.

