### Follow up

At week 16, the subject will be called or will visit the clinic to evaluate for any adverse effects of the drug. For subjects that may discontinue or withdraw early, we will record the rationale on final visit or via telephone conversation and cumulative curcumin dosage at that time point.

Table 2 shows the schedule of activities subjects will undergo in this study from beginning to end. Once the subject complete all phases of the study, indicated in Table 2, they are considered as completed the study.

**Table 2 Tab2:** Schedule of Activities that study subjects will go through from beginning to end

Procedures	Screening Day-7 to -1	Enrollment/baseline Visit 1, Day 1	Study visit 2 Week 4	Study visit 3 Week 8	Study visit 4 Week 12	Follow up Week 16
Informed consent	X					
Demographics	X					
Medical history	X					
Randomization		X				
Administer study intervention		X				
Concomitant medication review	X	X	X	X	X	
Physical exam (including height and weight)	X	X			X	
Vital signs	X	X			X	
ACT Scoring/ Questionnaire		X	X	X	X	
Spirometry (FVC, FEV1)		X	X	X	X	
Blood studies (eosinophils, IgE)		X			X	
Exhaled nitric oxide		X	X	X	X	
INR and PTT		X				
Urine pregnancy test (*if applicable)*		X	X	X	X	
Adverse event review and evaluation		X	X	X	X	X
Complete Forms	X	X	X	X	X	X

*ACT* Asthma control test, *FVC* forced vital capacity, *FEV1* forced expiratory volume in 1 s, *IgE* immunoglobulin E, *INR* international normalized ratio, *PTT* partial thromboplastin time

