### Data analysis

Assuming a 30% attrition rate, a sample size of 30 participants is estimated using a moderate effect size for the group x time interaction (f = 0.25 or partial η^2^ = 0.06), level of significance (α = 0.05), and power of 0.80. Effect size was calculated using GPower software (version 3.1.2, University of Dusseldorf, Dusseldorf, Germany).

Data will be summarized using mean and standard deviation for quantitative variables and counts (%) for qualitative variables. The normality of continuous variables will be examined using Shapiro Wilk’s test. The distribution of the participants’ characteristics by study group will be evaluated using chi-square for qualitative variables and independent t- test for quantitative variables. A 2-groupX 4-time points (baseline, week 4, week 8, and week 12) mixed factorial analysis of variance (ANOVA) will be used to examine changes in asthma control test scores, number of days missed from school/work, FEV1 (% predicted), FEV1/FVC ratio, FVC (% predicted), blood eosinophil count, blood total IgE, and FeNO levels by group over time.

There will two main analyses that will be conducted in this study. First: a comparison between study groups will be conducted by looking at group x time interaction effect. The interaction will be evaluated and if there is a statistical significance, an independent t-test will be used by comparing change from baseline between groups at each follow up. A post-hoc Bonferroni test will be conducted for the combined groups if the main effect of time in the mixed factorial found to be significant. Second: A one-way repeated measures, ANOVA, will be used for within-groups to test changes from baseline at each time point. A post hoc testing using Bonferroni test will be used on each group separately if the results of the one-way repeated measures, ANOVA, is found to be statistically significant.

The level of significance will be set at *p* ≤ 0.05. Statistical analysis will be performed using IBM SPSS Software version 25 for Windows (Chicago, IL, USA).

Safety endpoints will be analyzed as summary statistics during treatment. Adverse Events (AEs) will be counted once only for a given participant), presented by severity, frequency, and relationship of AEs with additional information regarding cumulative dosing. Adverse events leading to premature discontinuation from the study intervention and serious treatment-emergent AEs will be presented either in a table or a listing.

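### Outcome collection appears to stop when study drug stops, and replaced subjects have no stated place in the analysis, so the comparison is likely to become one of completers

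*Protocol article*

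**What the plan says.** Four parts of the protocol article bear on this.

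- **Discontinuation of study intervention.** "If the subject discontinued using curcumin, this will translate to discontinuation from the study". I read this as stopping study drug in either arm, since the trial is double blind. The sentence goes on to say that "remaining study procedures will follow as indicated by the protocol". Investigators may also withdraw a subject for non-compliance, for an adverse event, for "disease progression which requires discontinuation of the study intervention", or because the "participant is unable to receive curcumin tablets for 12 weeks". The data list begins "The data to be collected at the time of study intervention discontinuation will include the following: (1) reason for discontinuation of medication" and adds only side effects or symptoms and cumulative dose.
- **Follow up.** "For subjects that may discontinue or withdraw early, we will record the rationale on final visit or via telephone conversation and cumulative curcumin dosage". No asthma outcome is named here either.
- **Replacements.** Condition (2) replaces subjects who were "randomized, received the study intervention, and subsequently withdrew or withdrawn/discontinued from completing the study". Nothing says whether the replaced subject remains in the analysis.
- **Data analysis.** "Assuming a 30% attrition rate, a sample size of 30 participants" is estimated for a group by time interaction. The analyses are a 2 x 4 mixed factorial ANOVA and, within each group, a one-way repeated-measures ANOVA, in SPSS.

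The Design section gives 15 per arm. Methods and design explains that randomisation is there so that group differences can be put down to treatment alone.

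**The concern.** Randomisation protects the comparison only if subjects are kept in it, and measured, whatever happens to them afterwards. Here the events that end measurement (adverse events, worsening asthma, poor adherence) can depend on both treatment and outcome. If those subjects stop contributing asthma control, spirometry, FeNO and blood results, each arm is reduced to those who tolerated and completed 12 weeks, and the two sets of completers need not be comparable. For eosinophils and IgE the loss is total: Table 2 schedules bloods only at baseline and week 12, so an early leaver has no post-baseline value. A later analysis plan cannot recover outcomes that were never collected.

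There is also a smaller problem of clarity. The sample size already allows for 30% attrition, and the replacement rule provides for the same loss again.

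**Working it through.** **1. What follows from the text, and what is inferred.** Three things are written: stopping drug means discontinuation from the study; the data listed for leavers contain no efficacy outcome; treated leavers are replaced. One thing is inferred: that subjects with a missing visit drop out of the ANOVA. That is how a classical repeated-measures ANOVA works, but the article does not say so.

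**2. The plan's own figure.** Inputs from Data analysis: f = 0.25, α = 0.05, power 0.80, 2 groups, 4 time points, 30% attrition. The correlation between repeated measures, ρ, is not given, so I varied it. With λ = f²·N·4/(1 − ρ) and degrees of freedom 3 and 3(N − 2), rounding N to even:

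| ρ (assumed) | N for 80% power | N/0.7, rounded up |
|---|---|---|
| 0.50 | 24 | 35 |
| 0.55 | 22 | 32 |
| 0.60 | 20 | 29 |

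So 30 is reachable as a total that includes attrition if ρ is about 0.55 to 0.60. It cannot be confirmed, and it is not disputed here.

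**3. How many subjects are exposed to loss.**
- If 30 is the number randomised: 30 × 0.7 = 21 complete and 9 are lost.
- If leavers are replaced until 30 complete: 30/0.7 = 42.9, about 43 randomised, and 43 − 30 = 13 are lost.

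Either way about 30% of those randomised lie outside a completers' comparison.

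**4. Illustration of bias.** These are assumptions, not document figures. There is no true effect, and 15 completers per arm are analysed. In one arm 30% leave, and they would have been 1 SD worse than that arm's completers. In the other arm loss is unrelated to outcome.
- Bias = 0.30 × 1 SD = 0.30 SD.
- Single t-test, 28 df: noncentrality = 0.30 × √(15/2) = 0.82, so the two-sided rejection rate is 12.5% instead of 5%.
- Planned interaction F test, ρ = 0.5 assumed: λ = (15/2) × SS/(1 − ρ), where SS is the sum of squared deviations of the between-group differences over the four visits from their mean. If the bias grows linearly (0, 0.1, 0.2, 0.3), SS = 0.05, λ = 0.75 and the rejection rate is 9.6%. If it is constant after baseline (0, 0.3, 0.3, 0.3), SS = 0.0675, λ = 1.01 and the rate is 11.3%.

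**5. The two ends of the range.**
- Upper: the worst 30% of one arm leave. Bias = φ(−0.524)/0.7 = 0.50 SD. Treated as a pure shift, the t-test rejects 26% of the time. Truncation also shrinks that arm's SD to about 0.70, and simulating this gives about 33%. The interaction test, as a pure shift, gives about 19% to 25%.
- Lower: the worst 30% leave both arms alike. Simulated error is about 5%.

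**6. Power.** At f = 0.25 and ρ = 0.5, 21 complete cases give power 0.75. All 30 followed and analysed give 0.90, provided stopping drug does not dilute the effect.

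**The case against.** The strongest reply is that no sentence excludes anyone from the analysis. The analysis set and the handling of missing data commonly sit in an analysis plan, which is not shown. That stands, and it is why the conclusion is worded as likely rather than certain. It does not answer the part about collection, because an analysis plan works only on the data the protocol obtains.

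A reader might infer that replacement itself causes the bias. The documents do not support this. Randomization and blinding assigns the next sequential number, and nothing says that a replacement inherits the leaver's arm. Adding newly randomised subjects is harmless; losing the leavers' outcomes is not. Deleting the replacement rule alone would leave the selection as it is.

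A reader might also call the sentence in Discontinuation of study intervention self-contradictory. The clause on remaining procedures could mean that later visits continue, or only that the discontinuation data and final contact are obtained. It is ambiguous, and it must be reconciled with the rest of the section.

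Nor does replacement contradict the sample size. Allowance plus replacement is a redundancy that leaves the meaning of 30 open.

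Finally, this is a pilot, which limits how far its result will be relied on. But it is labelled a superiority trial and powered at 0.80 with significance tests, and arms of 15 are easily shifted by selective loss.

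**Conclusion.** The point holds in this form: followed as written, the rules are likely to turn the randomised comparison into one of completers, with about 9 of 30 or about 13 of 43 randomised subjects outside it, depending on what 30 means.

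The size and direction of any bias cannot be derived from the documents. The 30% shows exposure, not bias. The illustrative error rates (about 12% for one t-test and about 10% to 11% for the planned interaction test, at a 0.30 SD bias) rest on outcome-related loss in one arm only and, for the interaction test, on ρ = 0.5. Identical loss in both arms leaves the error near 5%. A reader might infer that the design favours curcumin; nothing in the text shows which arm would lose its poorer responders.

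**What to change.** 1. Reconcile Discontinuation of study intervention and Follow up so that stopping study drug does not end measurement. ACT, spirometry, FeNO, the week 12 bloods and the week 16 contact continue as scheduled unless the subject withdraws consent. The grounds for stopping drug are not touched.
2. In Replacements, state that any replacement counts as an additional randomised subject and that the replaced subject stays in the analysis in the assigned arm.
3. Analyse all randomised and treated subjects as assigned, with a mixed model for repeated measures (SPSS MIXED) using every available visit. This still assumes that data are missing at random, so it supports item 1 and does not replace it.
4. State whether 30 is the number randomised or the number completing, and keep one provision for attrition.

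The cost is amendment wording, a different SPSS procedure and some visits by subjects no longer on drug. Including those subjects may dilute the effect estimate. The change should be made before enrolment, because missed outcomes cannot be recovered later.

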### Lost to follow up

A subject is lost to follow up if they fail to return for scheduled visits and/or unable to be contacted and reached by the study site staff. We anticipate taking several additional and action measures when lost to follow up occurs such as counseling the subjects on the importance of the scheduled visit, willingness to continue and be part of the study, multiple telephone calls by the investigators, and mailing a letter to the last known address on file.

## Detailed Study procedure

### Baseline

After the subject(s) sign the informed consent, they will undergo history, physical exam including height and weight specifically cardiopulmonary examination, vital signs (blood pressure, heart rate, respiratory rate, and oxygen saturation), and an initial questionnaire that will include current asthma control test and demographics [16, 17]. Subjects will undergo randomization and will then be provided the curcumin or placebo. One member of the study staff will be responsible for randomization but will not share information regarding randomization with the subject nor study staff. Subject will undergo spirometry testing in the clinic site conducted by an experienced respiratory therapist or physician. Effort acceptance criteria is appropriate (American Thoracic Society Grade A—prefer 3 separate efforts with two largest FVC (Forced Vital Capacity) measurements with agreement within 150 mL, and FEV1 (Forced Expiratory Volume in the first second) agreement within 150 mL, B is acceptable if that is the best result after 8 efforts). Spirometer is handheld, and a calibration check will be performed daily with a 3L syringe prior to testing. In addition, Fraction of Exhaled Nitric Oxide (FeNO) will be collected and measured using NIOX VERO® Sensor machines.

Laboratory work will be obtained at the initial visit for plasma eosinophil count and serum total IgE, as well as baseline INR and PTT. Plasma eosinophil count will be drawn in approximately 1.5 mL of blood collected in a lavender top tube. IgE level is minimum 500 µL of blood, although 2 mL is preferred, collected in red tubes (serum) or light green tubes (lithium heparin). Plasma INR/PT and PTT will be collected in 3 mL blue-top tubes. Laboratory specimens will be analyzed via the Loma Linda University Medical Center Clinical Laboratory in compliance with the Clinical Laboratory Improvement Amendments (CLIA) of 1988. Urine pregnancy tests will be conducted for all applicable participants (i.e. females in reproductive age who are not currently on birth control) at baseline, and again at 4, 8 and 12 weeks.

### Visits 2 and 3

During subsequent visits (Weeks 4, 8), subjects will fill out a questionnaire that includes the Asthma Control Test which evaluates the number of severe asthma exacerbations patient has had including: worsening of symptoms for more than or equal to 48 h of consecutive bronchodilator use, any hospitalizations or emergency room visits [16, 17]. The questionnaire will also evaluate the number of missed days from school or work patient has had from asthma. Subjects will undergo spirometry testing in clinic which will be conducted by an experienced respiratory therapist or physician. Exhaled nitric oxide will be measured at that time as well.

### Visit 4

Subjects will fill out a questionnaire that includes the Asthma Control Test, evaluates the number of severe asthma exacerbations patient has had including worsening of symptoms for more than or equal to 48 h of consecutive bronchodilator use, any hospitalizations or emergency room visits. The questionnaire will also evaluate the number of missed days from school or work patient has had from asthma. Participant will undergo spirometry in clinic which will be conducted by an experienced respiratory therapist or physician. Exhaled nitric oxide will be measured at that time. Laboratory work will be obtained at this initial visit to measure plasma eosinophil count and serum total IgE.

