## Methods and design

This study will be a randomized, placebo controlled, double blinded pilot superiority phase 2 trial. The rationale for choosing a randomized, placebo control trial is to avoid bias in patient allocation-to-treatment and increase the probability that any differences between groups can be attributed only to the treatment. This study is a pilot study given that there is limited to no data that currently demonstrates curcumin as an effective treatment for asthma.

Recruited subjects will undergo a screening process to ensure they meet the following study criteria listed in Table 1.

**Table 1 Tab1:** Inclusion and exclusion criteria for the study

Inclusion criteria	Exclusion criteria
Male or female, aged 18 and older Physician diagnosed moderate to severe asthma: (GINA 2018) Stable asthma that requires ICS/LABA and/or an additional controller agent (i.e. LTRA, LAMA) Ability to take oral medication and be willing to adhere to the regimen Ability to speak and read English If female and sexually active, should use effective forms of birth control	Current use of turmeric (curcumin) or use within the last 7 days Current use of biologic therapy/immunotherapy/ or bronchothermoplasty Pregnancy or lactation Known allergic reactions to components of turmeric (curcumin) Current use of anticoagulants, and history of coagulopathy or liver disease INR greater than 2.0, PTT greater than 45.0 s

*GINA* Global initiative for asthma, *ICS* inhaled corticosteroids, *LABA* long-acting beta agonist, *LTRA* leukotriene receptor antagonist, *LAMA* long acting muscarinic, *INR* international normalized ratio, *PTT* partial thromboplastin time

All subjects will be screened to ensure meeting inclusion criteria. Screening failure is attained when a participant consents to participate but is not subsequently randomly assigned to either the study intervention or control. In addition, any individual who does not meet the criteria for participation due to meeting exclusion criteria (screening failure) maybe rescreened. Rescreened participants will be assigned the same participant number as for the initial screening.

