### Dosing and administration

Subjects will be receiving curcumin 1500 mg or matching placebo by mouth twice daily for the study period, 12 weeks. Any missed or vomited doses will be skipped and resumed at the next scheduled time. Subjects will use a dosing calendar to record administration or missed doses. The reason for selecting this dose is that curcumin (at 20 mg kg^−1^ bodyweight) was reported to attenuate allergen-induced airway hyper-responsiveness in sensitized guinea pigs [8]. It has been reported that humans can tolerate a dose of curcumin as high as 12 g/day, without any toxic side effects [15]. Therefore, we hypothesize that a dose of 3000 mg curcumin daily may significantly improve asthma control and affect other biomarkers of inflammation.

Sabinsa corporation will be providing the study drugs, both curcumin and matching placebo. Curcumin formulation will include 95% curcuminoids with black pepper extract plus inert excipients. The placebo formulation will contain the same inactive excipients found in curcumin. Both formulations will be identical in appearance. All study drugs will be clearly labeled for use for only this protocol and will not be shared or used for any patients not enrolled in this protocol. All study drug labels will include, *“Caution: New Drug Limited by Federal Law to Investigational Use."* Upon dispensing study drug will be labeled for subject specific use to be administered at home as prescribed by the investigator. All outpatient labels will follow California state Pharmacy laws for prescription drugs and be identified in a blinded fashion.

Study drugs will be stored at room temperature in their original containers for the length of time as instructed by the manufacturer Sabinsa as per their stability testing. Study drugs will be stored per Federal regulations, securely in limited-access pharmacy area and separately from commercial products. Storage temperature will be monitored daily by IDS to ensure proper storage is maintained.

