### Concomitant therapy

Current background standard of care treatment for asthma will continue during the study period. Medications to be reported in the Case Report Form are concomitant prescriptions medications, over-the-counter medications, and supplements. Any newly prescribed medications, over the counter or supplements are allowed except for curcumin. Concomitant therapy may affect the outcome as it can alter lab values and perceived side effects.

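### Pregnancy tests go only to women not on birth control, so a sexually active woman who follows the contraception criterion is never tested

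*Protocol article*

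**What the plan says.** Three parts of the protocol article bear on this.

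- **Eligibility (Methods and design, Table 1).** The inclusion column states: "If female and sexually active, should use effective forms of birth control". The exclusion column lists "Pregnancy or lactation".
- **Testing (Detailed Study procedure, Baseline).** Urine pregnancy tests are planned at baseline and at weeks 4, 8 and 12. The participants to be tested are defined, after an i.e., as "females in reproductive age who are not currently on birth control". Table 2 marks the same four visits with an if-applicable condition and gives no wider definition.
- **Withdrawal (Discontinuation of study intervention).** The investigator may withdraw a participant "if the participant meets an exclusion criterion (either newly developed or not previously recognized) that precludes further study participation". Pregnancy during the study falls under this ground.

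On dosing, the article states: "Subjects will be receiving curcumin 1500 mg or matching placebo by mouth twice daily for the study period, 12 weeks".

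**The concern.** Read together, the rules direct the test away from the women the contraception criterion is written for. Sexually active women are told to use contraception, and being on contraception removes them from testing. Those left to test are women of reproductive age without contraception, who are either not sexually active or not following Table 1.

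Contraceptive methods can fail, and early pregnancy is easily missed by history and examination. In a contraceptive user, a pregnancy present at entry or arising during treatment could go unnoticed while an investigational product continues to be taken. The article gives no reproductive-risk data for curcumin, so the size of any harm is unknown. The protocol itself, however, treats pregnancy as a reason not to take part.

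**Working it through.** The article states no figure to reproduce. The check sets the rules side by side and counts.

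**1. Scheduled tests.** The Baseline text gives baseline, week 4, week 8 and week 12, which is 4. Table 2 marks Visit 1 and weeks 4, 8 and 12, also 4. There is none at screening or week 16.

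**2. Who receives them.**

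| Woman of reproductive age | Meets the testing condition? | Tests |
|---|---|---|
| Sexually active, on contraception throughout (follows Table 1) | No, at any visit | 0 of 4 |
| Not sexually active, no contraception | Yes | 4 of 4 |
| Sexually active, no contraception (does not follow Table 1) | Yes | 4 of 4 |

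**3. What else could detect a pregnancy in the first row.**

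- *Physical examination.* Table 2 schedules it at screening, Visit 1 and week 12, so not at weeks 4 and 8. The Baseline text gives it a heart-and-lung focus.
- *Questionnaire.* As described under Visits 2 and 3 and Visit 4, it covers asthma control, exacerbations and missed days. No pregnancy item is mentioned.
- *Medication review.* Under Concomitant therapy, "Medications to be reported in the Case Report Form are concomitant prescriptions medications, over-the-counter medications, and supplements". This could show that a hormonal method was stopped, but not that a method failed.
- *Adverse event review and self-report.* These remain at every visit, and they depend on the woman already knowing or suspecting.

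**4. Length of the untested period.**

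- Dosing period: 12 weeks × 7 = 84 days, with no scheduled test for the compliant contraceptive user.
- Gap between tests for a tested woman: 4 weeks × 7 = 28 days.
- Daily dose in the active arm: 2 × 1500 mg = 3 g.
- Full course at complete adherence: 3 g × 84 = 252 g. One interval between tests: 3 g × 28 = 84 g.

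The gram figures show only how much product is taken without a scheduled check. They are not an estimate of fetal exposure. A tested woman who is not pregnant also takes 252 g over the course. The 252 g would be exposure in pregnancy only for a woman in the active arm who was pregnant throughout, fully adherent and never recognised. A urine test also misses the first days of a pregnancy, so 28 days is a gap between tests and not a ceiling on exposure.

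**5. Likely yield (assumption, since the article gives no count of contraceptive users).** Suppose 5 to 10 users among the 30 participants and an annual method failure rate of 1% to 10%:

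- Low: 5 × 0.01 × 12/52 = 0.01 pregnancies over the dosing period.
- High: 10 × 0.10 × 12/52 = 0.23.

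These cover both arms. With 1:1 allocation, about half would be in the active arm.

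**The case against.** The strongest reply is that the plan is coherent: contraception protects sexually active women, and tests cover women of reproductive age without it. Giving each group one layer of protection is a risk judgement and not an error. It stands that the rules do not conflict and that this is a choice. The choice is still open to criticism, because the layer given to contraceptive users has no check behind it although the check is already scheduled.

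A second reply is that the article condenses a fuller protocol that may define effective contraception and who is tested. That would answer a complaint about something left out. Here the article states an explicit rule with its own definition, and Table 2 does not widen it. The undefined term does matter for size: if birth control means hormonal methods only, barrier users would be tested and the gap shrinks, but hormonal users would still go untested.

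Third, part of the risk is already covered. The word currently can be read as status at each visit, so a woman who stops contraception becomes testable at the next one. This is fair. What remains is mainly method failure and unrecognised pregnancy at entry.

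Fourth, the week 12 test falls at the end of dosing and cannot shorten exposure. This is also right: of the four missed tests, only baseline, week 4 and week 8 could prevent or cut short dosing in pregnancy. The low expected yield stands too.

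**Conclusion.** The concern holds as a minor safety point. As written, a sexually active woman who follows Table 1 and stays on contraception has 0 of 4 scheduled pregnancy tests over 84 days of dosing, and three of those four could have limited exposure. For her, the pregnancy exclusion and the matching withdrawal ground have no scheduled test behind them.

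This rests on reading the i.e. as a definition and on birth control including whatever method she uses. The number of women affected and the reproductive risk of curcumin are not given, so the harm cannot be sized. Under the assumed ranges, the expected number of pregnancies during dosing is well below one. Sample size, endpoints and analysis are unaffected.

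**What to change.** In the Baseline section, redefine the tested group as *all females of childbearing potential, regardless of contraceptive use*, and define the if-applicable condition in Table 2 the same way. Keep the baseline and week 4, 8 and 12 tests, and have the baseline result available before randomisation. This wording also removes the need to settle what counts as birth control for testing purposes.

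The cost is two wording changes and up to four extra urine tests per contraceptive user, most of them low-yield, at visits already scheduled. With 5 to 10 such women, as assumed above, that is at most 5 × 4 = 20 to 10 × 4 = 40 tests across the trial.
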